### Statistical Analyses

Statistical methods, models, and procedures will be selected according to the research hypotheses being tested and the types of measures involved. We will set α<.05 as the level for statistical significance but will use appropriate corrections for multiple comparisons (eg, Bonferroni and Hochberg correction) to ensure that the actual overall effective type 1 error remains at a .05 level for the tests to be conducted. The frequency and patterns of missing data were carefully evaluated. To avoid potential bias resulting from missing data, imputation (eg, hot deck or multiple imputation) will be conducted, and statistical significance tests and modeling will be conducted with and without the imputed values. The findings from these analyses will be compared, and any difference will be evaluated. Potential nonlinear relationships between continuous predictors (eg, participants’ age) and outcomes (eg, CD4 count, viral load) will be evaluated through spline functions (eg, cubic spline) [22].

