### Sample Size Calculation and Power Analysis

Our proposed sample size is based on a comparison of the main outcome of linkage to HIV care between the study arms of the LINX App and LINX App Plus conditions based on a priori logistic regression sample size calculations in PASS 2008 software. Calculations assume linkage-to-care base rates across conditions of 70% based on 2013 estimates of linkage to care within 3 months of an HIV diagnosis for African American people. We also assume a type 1 error of .05 and type 2 error of .2 (or power 80%). Our targeted enrollment of 200 participants in each condition will give us enough power to detect a difference in HIV linkage between LINX App and LINX App Plus arms as low as 12.5%. In addition to comparisons between the 2 study arms as a dichotomous measure, we will also compare linkage to care and other outcomes by intervention dosage as a continuous measure. Comparisons of continuous measures often increase power analyses relative to comparison of dichotomous measures; this comparison is similarly anticipated to do so in our study.

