### Limitations: Engagement and Retention Challenges

This service should also help with a potential foreseeable challenge—the retention of participants. Study staff will develop a targeted retention plan that looks at maximizing every opportunity that the study staff may have when meeting participants. This includes walking participants through a process of updating multiple points of contact information and ensuring that participants have access to LINX LA so that efforts to promote engagement continue to reach participants. Another planned strategy includes tracking all contact with participants and identifying problems with communication at the earliest possible time point. For example, by reviewing weekly text message data, the staff can identify which participants have mobile phone numbers that may be out of service or otherwise may not be receiving study text messages.

Finally, although creative content developed by members of the community is a key strategy to driving traffic to LINX LA, the study will be challenged to command the attention of participants who currently spend time on other social media and web-based platforms. Given the significant investment in developing a mobile app for and by BSMM+, the study will need to remain nimble in its efforts to engage participants on the platform. Thus, an ongoing review of back-end user data, including analytics on usage patterns, combined with feedback provided by participants during assessments and coaching sessions must drive future strategies to retain an engaged pool of participants.

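### The 80% power claim is stated at an uncorrected .05, although the plan promises to hold the overall type 1 error at .05 across its tests; no attrition allowance is stated either

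*Protocol article*

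**What the plan says.** Under Sample Size Calculation and Power Analysis, the protocol article sizes the trial on one comparison, linkage to HIV care between the two arms. The inputs are:

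- Base rate: "Calculations assume linkage-to-care base rates across conditions of 70" percent.
- Error rates: "We also assume a type 1 error of .05 and type 2 error of .2 (or power 80" percent).
- Result: "Our targeted enrollment of 200 participants in each condition will give us enough power", the target being to "detect a difference in HIV linkage between LINX App and LINX App Plus arms as low as 12.5" percent.

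The section mentions neither a multiplicity correction nor an allowance for loss to follow-up.

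Under Statistical Analyses, the article commits to corrections for multiple comparisons, naming Bonferroni and Hochberg as examples, "to ensure that the actual overall effective type 1 error remains at a .05 level for the tests to be conducted". It does not say which tests form the family.

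The Primary Outcomes section names two outcomes, medication adherence and viral suppression. Table 1 adds technology use as a third. Linkage to care is in neither list. Under Limitations: Engagement and Retention Challenges, "the retention of participants" over the 12-month study is called a foreseeable challenge, with no rate given.

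**The concern.** Two statements in the same document do not fit together. One guarantees an overall error of .05 across several tests. The other computes power as if the single powered test had the whole .05 to itself. If alpha is shared, the power for that test is lower than stated and the smallest detectable difference is larger.

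What is at stake is how a null result is read. A reader who takes the 80% at face value would treat a non-significant comparison as fair evidence against a 12.5-point effect, when the plan's own error rule may leave a chance of missing such an effect nearer 25% to 30% than 20%. Loss over 12 months would widen the gap, and the article does not say whether 200 per arm already covers it.

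**Working it through.** **Inputs.** From the sample size section: 70% base rate, 12.5-point difference, alpha .05, power 80%, 200 per arm, 1:1. Sidedness and direction are not stated. I take a two-sided test and an improvement, p1 = .70 against p2 = .825, because this reproduces the stated figure best.

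**Formula** (pooled two-proportion test, n per arm, p̄ = .7625):

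power = Φ{ [d√n − z√(2p̄(1−p̄))] / √(p1(1−p1) + p2(1−p2)) }, where z is the two-sided critical value

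with √(2 × .7625 × .2375) = .6018 and √(.2100 + .1444) = .5953. For the continuity-corrected version, d is replaced by d − 1/n.

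**Step 1: the plan's own figure.** Required n = (1.960 × .6018 + .842 × .5953)² / .125² = 2.824 / .015625 = 180.8, so 181 per arm, or 197 with continuity correction. At 200 per arm, d√n = .125 × 14.142 = 1.768 and power = Φ[(1.768 − 1.180)/.5953] = Φ(.988) = 83.8%, or 80.8% with continuity correction. The stated figure holds at its own inputs. Other readings fit less well: a one-sided .05 needs 143 per arm, 70% against 57.5% needs 231, and rates centred on 70% need 210.

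**Step 2: Bonferroni, 200 per arm, no loss.** Values in brackets use the continuity correction.

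| Tests | Alpha | z | Power for 12.5 points | Detectable difference at 80% | n per arm for 12.5 points |
|---|---|---|---|---|---|
| 1 | .05 | 1.960 | 83.8% (80.8%) | 11.9 (12.4) points | 181 (197) |
| 2 | .025 | 2.241 | 75.9% (72.1%) | 13.0 (13.5) points | 220 (235) |
| 3 | .0167 | 2.394 | 70.9% (66.7%) | 13.6 (14.1) points | 242 (258) |

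For two tests, for example: (1.768 − 2.241 × .6018)/.5953 = .704 and Φ(.704) = 75.9%.

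**Step 3: Hochberg, 200 per arm, no loss.** I simulated 1,000,000 draws of normal test statistics, with mean 1.960 + .988 = 2.948 for the powered outcome and correlation 0 or .5 between outcomes.

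- Other outcomes null: about 76% (two outcomes) or 71% (three).
- Other outcomes with equally strong effects: 82% to 83% (two) or 80% to 81% (three).

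**Step 4: attrition.** No rate is stated. One possibility is that 200 is the continuity-corrected requirement with almost no margin (197). Another is that it is 181 inflated for about 10% loss: 181 × 1.10 = 199.1, so 200, or 181/.90 = 201.1, so 202. On the second reading, 180 per arm are evaluable and d√n = .125 × 13.416 = 1.677. Without continuity correction:

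| Alpha | Power at 180 per arm |
|---|---|
| .05 | 79.8% |
| .025 | 70.9% |
| .0167 | 65.4% |

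At 180 per arm, Hochberg gives 77% to 78% (two outcomes) or 75% to 76% (three), even with equally strong effects on the others.

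**The case against.** Four points can be made for the plan, and each limits the conclusion.

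- **A reader might infer that the calculation is wrong.** It is not. It reproduces at its stated inputs, and using .05 for a single comparison is not a miscalculation. The defect is that it is not reconciled with the correction promised elsewhere.
- **A reader might infer that the plan corrects over its two or three primary outcomes.** It does not say so. It speaks only of the tests to be run and gives the two methods as examples. Two and three tests are my illustration, and the family may be fixed in an analysis plan that is not shown. Linkage, the powered outcome, is in neither primary list; if it joined, the family would have three or four members.
- **A reader might infer that the 80% is certainly missed.** That holds under Bonferroni at 200 per arm. Under Hochberg with full retention, power stays at about 80% or more if the other outcomes have comparably strong effects. The article does not state that condition.
- **A reader might infer that no attrition was allowed for.** That is not established, because 200 also fits 181 plus about 10%. Missed interviews need not mean lost outcomes either, since adherence and viral suppression also draw on medical records and imputation is planned. All that can be said is that no allowance is stated.

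None of this removes the conflict. Reading 200 as already inflated leaves fewer evaluable participants, and so less power at any corrected alpha.

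**Conclusion.** The concern holds as an inconsistency between the error-control promise and the power statement. At 200 per arm with no loss, Bonferroni brings the claimed 80% for 12.5 points down to about 76% for two tests or 71% for three (72% or 67% with continuity correction). In effect-size terms the shift is modest: about 13.0 or 13.6 points, or 13.5 or 14.1 with continuity correction, against the stated 12.5. Under Hochberg the 80% depends on effects on the other outcomes. If 200 includes about 10% loss, power at .025 and .0167 is 71% and 65%.

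These figures assume a two-sided test, 70% against 82.5%, and families of two or three tests. They are also power for linkage to care, because that is the only outcome with a stated base rate and difference. The article states no power for adherence or viral suppression, and the figures should not be carried over to them.

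**What to change.** Either of two changes would do, and neither needs extra participants.

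1. **Keep the correction and restate the power.** Name the outcomes in the corrected family and the method. Say whether linkage to care belongs to it, and reconcile this with the two primary lists. Then give the power or detectable difference at the corrected alpha, on the expected evaluable number per arm with the assumed loss stated, using a base rate for the outcome actually tested.
2. **Order the tests.** Name one primary outcome to be tested first at the full two-sided .05, with the others tested only if it succeeds, and recompute power for that outcome with its own base rate and evaluable number. The overall error stays at .05 without splitting alpha. The small downside is that later outcomes can be claimed only if the first is significant.

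The choice between them is partly preference. Either costs a few sentences and one recalculation. The 70% linkage rate should not be reused for a different lead outcome.

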## Results

### Expected Outcomes

The strengths of this trial are rooted in its work to address the effect of HIV among a group of individuals hit hard by the epidemic. In LAC, BSMM are facing an increase in the numbers of new HIV diagnoses, and linkage to care has historically been a specific challenge for these men. The high level of need provides an opportunity to make a measurable impact through this trial. The intervention’s focus on social services and legal needs is distinct. Although structural barriers are resistant to change and require sustained efforts, including advocacy at a policy level, specific assistance provided to ameliorate the effects of these barriers is achievable. This work will be a defining hallmark of the intervention. Finally, the use of mobile technology to foster a voice and a collective identity across BSMM+ and as an avenue for accessing resources and promoting social support, although not new, is still a strategy worth exploring.

The LINX LA study’s contribution will be to increase the understanding of how to develop technology for and by the communities targeted by an intervention and how to establish programmatic structures to ensure that the platform maintains a strengths-based lens in lifting voices from the same community. Investment in such strategies has the potential to improve ART adherence and increase viral suppression among BSMM+.

### Expected Timeline

The LINX App was completed and recruitment and enrollment for the trial started in May 2018 on a rolling basis. Owing to the outbreak of COVID-19, the collection of survey data at 3 time points over 12 months will pose a challenge. Nonetheless, the length of the study per patient will be 12 months. We expect to complete data collection 12 months after the last participant has been enrolled in the study, that is, by January 2021, and plan the dissemination of results subsequently.

## Discussion

### Limitations: Recruitment Challenges

There are potential challenges to this trial. It employs convenience sampling techniques to recruit the target population, which limits generalizability. In addition, if recruitment fails to yield the required number of participants, we may not have adequate statistical power to detect effects of intervention conditions on outcomes. To address these uncertainties, we plan to compare our sample to data from other projects focused on BSMM+ in LAC. The LAC Division of HIV and STD Programs has implemented a clinic-based medical care coordination (MCC) program to increase viral suppression (VS; <200 c/mL) among people living with HIV at high risk for poor health outcomes (eg, diagnosed with HIV in the past 6 months, on ART without VS, out of care for more than 6 months). The MCC program collects clinical data across 35 Ryan White Program–funded clinics across the county serving these populations, including those that identify with our target population. Comparing results from the study with data from participants in the county’s MCC program will help to address this gap.

Recruitment of BSMM+ may be challenging in LAC due to the sheer size of the county and the study’s eligibility criteria, requiring participants to be both living with HIV and identifying as a sexual minority. For this reason, study staff will implement a diverse set of strategies to engage varied audiences during the recruitment period, including web-based efforts and in-person efforts detailed in Textbox 1. The study will also offer participants with transportation assistance. By providing access to ride-sharing resources through Lyft Concierge services, participants will be able to meet study staff at the location of their choice. This additional support has proven effective in reducing the number of cancelled meetings between study staff and participants [18].

### Limitations: Engagement and Retention Challenges

This service should also help with a potential foreseeable challenge—the retention of participants. Study staff will develop a targeted retention plan that looks at maximizing every opportunity that the study staff may have when meeting participants. This includes walking participants through a process of updating multiple points of contact information and ensuring that participants have access to LINX LA so that efforts to promote engagement continue to reach participants. Another planned strategy includes tracking all contact with participants and identifying problems with communication at the earliest possible time point. For example, by reviewing weekly text message data, the staff can identify which participants have mobile phone numbers that may be out of service or otherwise may not be receiving study text messages.

Finally, although creative content developed by members of the community is a key strategy to driving traffic to LINX LA, the study will be challenged to command the attention of participants who currently spend time on other social media and web-based platforms. Given the significant investment in developing a mobile app for and by BSMM+, the study will need to remain nimble in its efforts to engage participants on the platform. Thus, an ongoing review of back-end user data, including analytics on usage patterns, combined with feedback provided by participants during assessments and coaching sessions must drive future strategies to retain an engaged pool of participants.

## Abbreviations

AMAAD: Arming Minorities Against Addition and Disease Institute
ART: antiretroviral therapy
BSMM: black sexual minority men
CAB: Community Advisory Board
CD4: cluster of differentiation 4
IRB: institutional review board
LAC: Los Angeles County
LGBTQ: lesbian, gay, bisexual, transgender, and queer
LINX App: LINX web-based mobile app arm
LINX App Plus: LINX web-based mobile app with LINX Coach arm
LINX LA: LINX web-based mobile app
MCC: medical care coordination
UCLA: University of California, Los Angeles
VS: viral suppression
